#### Classroom observations

To examine quality of the preschool environment, classroom observations will be conducted in both LEAPS classrooms and comparison preschool classrooms. As LEAPS schools are by design typically the only preschool service operating in an intervention cluster, in order to select the most suitable comparison, the comparison preschool classrooms will be selected based on the following: (i) location: school should be located as close to the LEAPS evaluation cluster as possible; and (ii) prioritizing enrollment of government schools (standard service) where available, followed by NCHD-operated schools and other options (private/Madrasa) to reflect the distribution of these types of schools in rural communities in the targeted districts. Comparison classrooms may vary with respect to the preschool classroom arrangements, including grade-level groupings (stand-alone preschool classrooms or multi-grade classrooms), single- or mixed-gender classroom, and informal or formal settings. One comparison classroom teacher will be enrolled for each LEAPS school. All Step 1 and Step 2 LEAPS schools (*n* = 66) and equivalent number of comparison schools will be observed at two timepoints: once in Step 2 (mos. 14–16) and once during Step 3 (mos. 21–24). All Step 3 LEAPS schools (*n* = 33) and equivalent number of comparison schools will be observed at one timepoint in Step 3 (mos. 21–24).
Eligibility criteria:
◦ LEAPS school: Must be located in an intervention cluster.◦ Comparison preschools: Fits criteria for location, type of school, and gender make-up.Exclusion criteria: None

#### Implementation, costing, and systems strengthening evaluations

A phenomenological design will be employed to collect original qualitative data in addition to administrative and programmatic data, Global Positioning System (GPS) and location data, and costing data to inform the concurrent mixed-methods implementation evaluation, cost evaluation, and systems strengthening evaluation (all three of which are described in detail in the sub-sections below). Data for these activities will be collected in mos. 22 to 24 at the end of Step 3. Participants in qualitative data collection activities will be purposefully sampled to reflect variation in district, demographics, and stakeholder role. Qualitative data collection will include focus group discussions (FGDs) and in-depth interviews (IDIs). Administrative, classroom, and programmatic data will be collected from NCHD district offices and around training and supervision activities. Costing data will be collected from internal project budgets (NCHD program and university research partners).
Eligibility criteria: Sampling and participant details for qualitative data collection are detailed in Table 2Exclusion criteria: Participants demonstrate signs of severe clinical health condition or disability

**Table 2 Tab2:** Qualitative data collection activities and participants. Table 2 summarizes planned qualitative data collection activities by stakeholder, including sampling details. FGD = Focus Group Discussion, IDI = In-depth Interview

Stakeholder	No. of IDIs/ FGDs	Participant sampling
CYLs	4 FGDs	• Representation from all districts and steps • Maximize variation in CYL age, marital status, education, parenting status
CYLs	16–17 IDIs	• Representation from all districts and steps • Variation in marital status, parenting status, age, and urbanicity
CYLs’ families	4 Family Interviews	• Sub-set families of the same CYLs in IDIs • Variation in marital status and family structure
Children’s mothers	4 FGDs	• Representation from all districts • Child must be enrolled in LEAPS preschool • From rural communities
Children’s fathers	4 FGDS	• Representation from all districts • Child must be enrolled in LEAPS preschool • From rural communities
NCHD Feeder school teachers	4 FGDs	• Representation from all districts and steps
NCHD field officers	4 FGDs	• Representation from all districts and Steps • All female field officers will be enrolled • Variation in number of supervisees
NCHD master trainers	1 FGD	• Including all field officers who have been selected as master trainers
LIST team	1 FGD	• Including the LIST members
LIST members	1 FGD (Pile sorting activity)	• Including the LIST members
NCHD district team managers	1–2 FGDs	• Including all NCHD district managers
District stakeholders	4–8 IDIs	Sample most relevant/influential stakeholders per district as per Intervention Team’s inputs: • Village leaders • District government officials • Social Welfare Department • Education Department

##### Implementation evaluation

Implementation evaluations are critical in transition-to-scale research for a number of reasons: (i) implementation evaluations provide key insights on the challenges of scaling up, in terms of replicability, coverage, appropriate monitoring and evaluation and sustainability [39]; (ii) they help to explain why certain results were achieved, specifically, understanding which components of the intervention contributed to observed impact [41]; (iii) they help to make effectiveness results more interpretable and to avoid type III error, i.e., evaluating an intervention that has not been adequately implemented and therefore drawing incorrect conclusions about an intervention’s effectiveness [42]; and (iv) they are tools to assess the quality and accuracy of the intervention delivered to participants. This trial’s implementation evaluation will capture information relating to facilitators and barriers for participation in and delivery of LEAPS, as well as fidelity to the LEAPS program model and the quality of the ECCE and youth vocational training services delivered. In doing so, we seek to better understand the processes and conditions required to support program expansion, replication, and sustainable scale-up.

##### Cost evaluation

Attention to cost-effectiveness of interventions is a crucial component of intervention planning and evaluation, particularly in resource-limited contexts [41]. The LEAPS cost evaluation will provide information about costs to government providers to inform strategies for program expansion and replication. This evaluation will apply an ingredients approach to assessing program costs, cost per beneficiary, and cost per impact [43].

##### Systems strengthening evaluation

This component of the study aims to evaluate the readiness of NCHD to uptake LEAPS for sustainable scaling and replication for expansion in Sindh and other provinces in Pakistan. Our research team will be facilitating a workshop series for NCHD to provide technical capacity building around organizational capacities identified as central to sustainable, quality implementation of LEAPS. Six “pillars” for systems strengthening were identified based on a review of frameworks for supporting, monitoring, and evaluating organizational capacity development [44–47], transition readiness [48–50], and community-based management training [51, 52], and informed by inputs and feedback from the NCHD provided during a needs assessment conducted by the research team. The LEAPS System Strengthening Pillars include (i) training, (ii) supervision, (iii) monitoring and evaluation, (iv) leadership and governance, (v) advocacy and communication, and (vi) financing and resource mobilization. A set of indicators will be co-created with NCHD and used to assess NCHD’s “systems readiness” across each pillar. The systems strengthening evaluation has three aims: (i) to identify barriers and enablers for implementation at scale; (ii) to assess the effectiveness of the capacity development strategy on NCHD’s competencies related to the LEAPS System Strengthening Pillars; and (iii) to evaluate efforts of advocacy in NCHD with partners for replication, expansion, and investment (e.g., awareness about ECCE and youth development, enactment of policies, funding commitments made, sustainability plan developed).

### Outcomes, mediators, and covariates

The trial’s primary and secondary outcomes and covariates are described in Table 3. All measures will be adapted and piloted for the local socio-cultural and language context [53]. The classroom observation tool will be adapted for use in LEAPS from the Measure of Early Learning Environments (MELE) module of the Measuring Early Learning Quality and Outcomes (MELQO) tool [54] and the Instrument for Measuring Quality of Early Childhood Education in Colombia (IMCEIC) [55]. Targeted outcomes and covariates are selected to align with the LEAPS program theory of change (see Fig. 4).

**Table 3 Tab3:** Description of trial outcomes, assessment tools, mediators, and covariates. *The starred IDELA, executive functioning skills assessments, anthropometric, and demographic measures were previously adapted for the rural Pakistan context for use in the LEAPS efficacy trial [26]. **The SRQ-20 was previously adapted and validated for use in rural Pakistan [56]. All other measures were adapted or developed for use in this trial. All outcomes will be recorded as absolute values, and cluster-level outcomes will be aggregated by averaging the individual outcomes within each cluster

Variable	Tool	Description
***Primary outcome***		
School Readiness	International Development & Early Learning Assessment (IDELA) [31]*	IDELA assesses the development and early learning, namely school readiness, of young children aged 3.5–6 years old. The tool includes sub-tests for emergent math, socio-emotional development, emergent literacy, and motor skills. The primary outcome will be the IDELA total score, which will be the parameter estimates computed through a Graded Response Model based on the recommendation of the tool developers. Higher scores reflect better outcomes.
***Secondary outcomes***		
Emergent Math	International Development & Early Learning Assessment (IDELA) [31]*	IDELA subdomain comprising seven sub-tasks assessing emergent math skills. The domain score is computed through a Graded Response Model recommended by the tool developers. Higher scores reflect better outcomes.
Socio-emotional Development	International Development & Early Learning Assessment (IDELA) [31]*	IDELA subdomain comprising five sub-tasks assessing socio-emotional development. The domain score is computed through a Graded Response Model recommended by the tool developers. Higher scores reflect better outcomes.
Emergent Literacy	International Development & Early Learning Assessment (IDELA) [31]*	IDELA subdomain comprising six sub-tasks assessing emergent literacy skills. The domain score is computed through a Graded Response Model recommended by the tool developers. Higher scores reflect better outcomes.
Motor Skills	International Development & Early Learning Assessment (IDELA) [31]*	IDELA subdomain comprising four sub-tasks assessing fine and gross motor skills. The domain score is computed through a Graded Response Model as recommended by the tool developers. Higher scores reflect better outcomes.
Child Executive Functioning Skills: Working Memory	Corsi Block-Tapping Test [57]*	Direct assessment of child’s working memory skills. The child’s score reflects the longest sequence for which two block series were repeated correctly, plus 0.5 if one longer series was also correctly processed (range 0–4 points). Higher scores indicate better outcomes.
Child Executive Functioning Skills: Inhibitory Control	Knock and Tap assessment [58]*	Direct assessment of child's inhibitory control skills. Total score is the sum across 16 items (range 0–16 points). Higher scores reflect better outcomes.
	Peg Tap assessment [58]*	Direct assessment of child’s inhibitory control skills (range 0–16 points). Total score is the sum across 16 items. Higher scores reflect better outcomes.
Child Executive Functioning Skills: Cognitive Flexibility	Dimensional Change Card Sort [59, 60]*	Direct assessment of child’s cognitive flexibility skills. Five sub-scores will be examined: total number correct trials on the separated level, pre- and post-switch (0–6 points each); total number correct trials on the integrated level, pre- and post-switch (0–6 points each); and total correct on the border version (0–12 points). Higher scores reflect better outcomes.
Child General Executive Functioning Skills	Head Toes Knees Shoulders task [61]*	Direct assessment of child’s general executive functioning skills. The assessment contains two sections. Child participants may receive 0 to 20 points for each section. Scores will be presented separately for each section. Higher scores reflect better outcomes.
Youth Executive Functioning Skills: Working Memory	Backward Word Span Task [62]*	Direct assessment of youth’s working memory skills. The participant’s score reflects the longest sequence for which two series were repeated correctly, plus 0.5 if one longer series was also correctly processed (range 0–6 points). Higher scores reflect better outcomes.
	Corsi Block-Tapping Test [63]*	Direct assessment of youth’s working memory capacity. Participants will be administered two tests: a forward and a backward test. A score will be awarded for each test, reflecting the longest sequence for which two series were repeated correctly, plus 0.5 if one longer series was also correctly processed (range for each 0–7 points). Scores will be presented separately for each test. Higher scores reflect better outcomes.
Youth Executive Functioning Skills: Inhibitory Control	Number Stroop Effect [64]*	Direct assessment of youth’s inhibitory control skills. Points are summed across 20 items to calculate the overall sum score (range 0–20 points). Higher scores reflect better outcomes.
Youth Executive Functioning Skills: Cognitive Flexibility	Trail Making Task (TMT) [65, 66]	Direct assessment of youth’s cognitive flexibility skills. cores reflect the time for completion in seconds, with the maximum time limit being 300 s (range 0–300). Lower scores indicate a better outcome.
Youth Personal and Professional Development	Self-reported Questionnaire	Self-reported questionnaire developed for study context which includes items examining aspects of professional and personal development pertaining to autonomy, self-efficacy, self-esteem, professional growth, and aspirations. Mean item scores will be calculated for each domain. This does not include a standardized scale.
Youth Self-Reported Depressive Symptoms	Self-Reporting Questionnaire 20-Item (SRQ-20) [67]**	Direct assessment of youth self-reported depressive symptoms over the last 30 days. Items are summed for a total score of depressive symptoms over the last 30 days (range 0–20 points). Higher scores reflect poorer outcomes.
***Mediator***		
Classroom Structural and Process Quality	To be adapted from the Measure of Early Learning Environments (MELE) module of the Measuring Early Learning Quality and Outcomes (MELQO) tool [54] and the Instrument for Measuring Quality of Early Childhood Education in Colombia (IMCEIC) [55]	Direct Assessment of children’s pre-primary learning environments in LEAPS preschool and comparison classrooms. The 7 major domains are: environment and physical setting, family and community engagement, personnel, interactions, inclusiveness, pedagogy, and play. Mean scores will be calculated from all items (range 1–4 points). Higher scores reflect better outcomes.
***Covariates***		
Child's Household Demographics	Child Household Questionnaire, including Socio-Economic Status Index [68]*; Household Food Insecurity Access Scale (HFIAS) [69]*	Household questionnaire including items examining child’s age, child’s gender, parental education, parental employment, assets-based household socio-economic status, and household food insecurity.
Child Anthropometric Indices	Anthropometric Questionnaire*	Anthropometric Questionnaire collects child age and child growth indicators. Child’s anthropometric *z* scores will be calculated using WHO Child Growth Standards.
Youth’s Household Demographics	Youth Enrollment Questionnaire, including Socio-Economic Status Index [68]*; Household Food Insecurity Access Scale (HFIAS) [69]*	Youth Enrollment Questionnaire including items examining the youth’s demographics, such as age, education, marriage status, assets-based household socio-economic status, and household food insecurity.

**Fig. 4 Fig4:**
[figure not shown]
LEAPS program theory of change

### Sample size and power calculation for stepped wedge cluster-randomized trial

A power calculation was conducted with respect to the changes in average child outcomes using representative population surveys, applying the methods as outlined by Hemming and Taljaard [70]. The primary study outcome is children’s school readiness as indexed by scores on the International Development and Early Learning Assessment (IDELA). An intraclass correlation coefficient (ICC) of 0.175 was calculated based on the results of the LEAPS efficacy trial [26] using total IDELA score at endline for the control group. With a fixed number of clusters (*n* = 99) and a step-size of three (*n* = 33 clusters randomized per step), we estimate that at least 8 children per cluster per round, or 792 children total per round, will need to be enrolled to detect a 0.3 SD effect size at 80% power. To achieve adequate power and take refusal rate into account, we will enroll 11 child-caregiver dyads per cluster for a total of 1089 child-caregiver dyads per round, which should detect a 0.3 SD effect size at 90% power with full recruitment. In other words, we estimated sufficient sample sizes to achieve at least 80% power with up to 30% refusal/under-recruitment rate in each round of the data collection under the intent-to-treat principle. This includes refusals from caregivers and children, or under-recruitment due to a decrease in children available at the point of data collection, particularly in smaller villages.

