**Methods:**

We use a stepped wedge cluster-randomized trial to evaluate implementation of LEAPS. Ninety-nine clusters will be randomized to receive the intervention in one of three 7-month steps (33 clusters/step). The primary outcome is children’s school readiness (indexed by the total score on the International Development and Early Learning Assessment (IDELA)). Secondary child outcomes are children’s IDELA domain scores and executive functions. Data are collected in cross-sectional surveys of 1089 children (11 children/cluster from 99 clusters) aged 4.5–5.5 years at four timepoints (baseline and at the end of each step). Additionally, we will enroll three non-randomized youth participant open cohorts, one per step (33 CYLs: 66 comparison youth per cohort; 99:198 in total). Youth cohorts will be assessed at enrollment and every 7 months thereafter to measure secondary outcomes of youth personal and professional development, depressive symptoms, and executive functions. A non-randomized school cohort of 330 LEAPS students (10 students/cluster from 33 clusters) will also be enrolled and assessed during Step 1 after intervention rollout and at endline. The quality of the learning environment will be assessed in each LEAPS ECCE center and in a comparison center at two timepoints midway following rollout and at endline. A concurrent mixed-methods implementation evaluation will assess program fidelity and quality, and the extent to which a technical support strategy is successful in strengthening systems for program expansion. A cost evaluation will assess cost per beneficiary. Data collection for implementation and cost evaluations will occur in Step 3.

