#### Population survey

A cross-sectional survey of child-caregiver dyads will be conducted at four timepoints: at baseline (Step 0; mos. 1–3) and again at the end of each consecutive step, with 7 months between data collection rounds. Eleven children aged 4.5–5.5 years and their caregivers will be enrolled in the population survey from each of the 99 clusters (1089 child-caregiver dyads total), regardless of the child’s enrollment in the LEAPS preschool program. The primary objective of the population survey will be to assess changes in the average school-readiness over time. With this trial design, rather than assessing program impact on specific individuals, we are aiming to assess the impact of LEAPS on local (cluster-level) school readiness, which is a function of both the proportion attending LEAPS and the impact on the treated. By including both LEAPS participants and children who are not participating in the LEAPS program, this design will allow us to separate treatment effects on the treated from average (intent-to-treat) effects at the population level. The sample will be drawn from village birth registries provided by NCHD, which will be verified (a) by cross-checking against birth registries from local community health workers; and (b) through household visits conducted by research team members. The sample will be re-drawn at each of the four data collection timepoints. Children may be enrolled for assessment at multiple timepoints. Assessors will use a random number generator to select 11 participants/cluster using the verified lists of eligible children prepared for each cluster. If a participant refuses, assessors will select the next participant in the random sequence.
Eligibility criteria: Child is age 4.5–5.5 years ± 2 weeks (i.e., 53.5–66.5 months at the time of the survey) and resides in the targeted villageExclusion criteria: Child or caregiver shows signs of severe clinical health condition or disability

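### The stated power (80% with 8 children per cluster, 90% with 11) does not follow from the protocol's own inputs, which give about 99.9% for both

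*Protocol article*

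**What the plan says.** All statements are in the protocol article.

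- **Design size** (Sample size and power calculation): "With a fixed number of clusters (*n* = 99) and a step-size of three (*n* = 33 clusters randomized per step").
- **Correlation** (same section): "An intraclass correlation coefficient (ICC) of 0.175 was calculated based on the results of the LEAPS efficacy trial".
- **Minimum sample** (same section): "at least 8 children per cluster per round, or 792 children total per round, will need to be enrolled" to detect 0.3 SD at 80% power.
- **Planned sample** (same section): 11 per cluster, 1089 per round, "which should detect a 0.3 SD effect size at 90% power with full recruitment".
- **Tolerated loss** (same section): the sample is said to give "at least 80% power with up to 30% refusal/under-recruitment rate" in each round.
- **Rounds** (Abstract, Methods): children "aged 4.5–5.5 years at four timepoints (baseline and at the end of each step"). The Population survey section adds: "The sample will be re-drawn at each of the four data collection timepoints".
- **Analysis model** (Impact evaluation): the Hussey and Hughes framework, with a random cluster effect, fixed time, a fixed effect for randomization stratum and an exchangeable correlation structure.

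The section gives no significance level, no cluster autocorrelation, and no statement that any cluster-period is left out.

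**The concern.** A stepped wedge with 99 clusters measured four times carries a great deal of within-cluster information. Needing 8 children per cluster per round to reach only 80% power for 0.3 SD looks far too pessimistic at an ICC of 0.175. If the printed power is wrong, so are the stated reason for 8 and 11 children, the statement about tolerable under-recruitment, and any impression a reader forms of how small an effect the trial can detect. The tolerated loss also looks inconsistent with the stated minimum, whatever model is used.

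**Working it through.** **Inputs.** From the protocol: I = 99 clusters, 33 per sequence; T = 4 rounds; ICC 0.175; effect 0.3 SD; m = 8 or 11 children per cluster per round. With total variance 1, τ² = 0.175 and σ² = 0.825/m. Assumed: two-sided alpha 0.05.

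**Formula (Hussey–Hughes, cluster-period means).**

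Var = Iσ²(σ² + Tτ²) / [(IU − W)σ² + (U² + ITU − TW − IV)τ²]

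- U = 33 × (3 + 2 + 1) = 198
- W = 33² + 66² + 99² = 15,246
- V = 33 × (9 + 4 + 1) = 462
- IU − W = 19,602 − 15,246 = 4,356
- U² + ITU − TW − IV = 39,204 + 78,408 − 60,984 − 45,738 = 10,890

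**m = 8.** σ² = 0.103125. Var = 99 × 0.103125 × 0.803125 / (449.21 + 1905.75) = 8.1994 / 2354.96 = 0.003482, so SE = 0.0590. Power = Φ(0.3/0.0590 − 1.96) = Φ(3.12) = 99.9%.

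**m = 11.** σ² = 0.075. Var = 99 × 0.075 × 0.775 / (326.70 + 1905.75) = 5.7544 / 2232.45 = 0.002578, so SE = 0.0508. Power = Φ(3.95), above 99.9%.

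**Attempt to reproduce the printed 80% and 90%.**

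| Calculation | 8 children | 11 children |
|---|---|---|
| Printed | 80% | 90% |
| Stated inputs and model | 99.9% | >99.9% |
| Same, autocorrelation 0.5 | 97.8% | 98.9% |
| Same, autocorrelation 0 | 96.5% | 97.8% |
| Single-period parallel, 99 clusters, 1:1 | 80.8% | 84.7% |
| 33 clusters in total (11 per step) | 83.5% | 92.7% |
| 33 clusters in total, autocorrelation 0.95 | 80.8% | 90.0% |
| 99 clusters, transition cells dropped | 87.7% | 95.1% |
| 99 clusters, transition cells dropped, autocorrelation 0.88–0.90 | 82–83% | 90–91% |

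In the rows with an autocorrelation, the cluster variance is split into a part constant over rounds (0.175 × autocorrelation) and a round-specific remainder. On a grid from 0 to 1 with all cells kept, the lowest power is 96.2% for 8 children and 97.6% for 11, at autocorrelations of about 0.1. A t reference distribution leaves 99.9% for 8 children. Alpha 0.001 still gives 96.4%.

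**Smallest adequate sample on the stated inputs.** m = 2 gives 77.3% and m = 3 gives 90.0%, so 3 children per cluster per round pass 80%.

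**Detectable effect at 80% power**, (1.960 + 0.842) × SE: 2.802 × 0.0590 = 0.165 SD with 8 children, and 2.802 × 0.0508 = 0.142 SD with 11. At autocorrelation 0 these rise to about 0.22 and 0.21 SD.

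**Tolerated loss.** 11 × 0.7 = 7.7 children per cluster and 1089 × 0.7 = 762 per round, against the stated minimum of 8 and 792. On the stated inputs, 7.7 children still give 99.9% power.

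**The case against.** The best defence is that the calculation used 99 clusters with assumptions the article leaves out. Table 1 places a transition period in the final two months of Steps 0, 1 and 2, and the surveys fall at the end of each step. Dropping each sequence's last pre-rollout cell and assuming an autocorrelation of about 0.88–0.90 comes close to both printed figures. Such details may also sit in the full protocol, which is not shown. This stands as a possible history, but it does not rescue the text. Table 1 labels those cells as control, every cluster is surveyed in every round, and the planned model has a single cluster effect. Dropping the cells under that model still gives 87.7% and 95.1%.

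A reader might infer that 33 per step was entered as the total number of clusters. That also comes close, and 8 is then the smallest sample reaching 80%. But the plain calculation gives 83.5% and 92.7%, and it matches both figures closely only with further unstated assumptions. The documents do not single out this cause.

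A reader might also infer that the trial is weak for its real target, because the Population survey section calls cluster-level readiness something "which is a function of both the proportion attending LEAPS and the impact on the treated", so that 0.3 SD would be diluted by attendance. The sample size section does not say that 0.3 SD came from the pilot. The account of the pilot does not say whether its effect was measured in attenders only. No attendance rate is given. The documents do not support a figure for dilution.

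Finally, the section says the sample detects 0.3 SD. It does not call that the smallest detectable effect, so a claim that a null result will be misread goes too far.

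**Conclusion.** The printed power and the minimum of 8 children are wrong as written. On the stated inputs and planned model, power is 99.9% and above 99.9% rather than 80% and 90%, and the detectable effect at 80% power is 0.165 SD (8 children) or 0.142 SD (11). How far below 0.3 SD it lies depends on the autocorrelation; at 0 it is still only about 0.22 and 0.21 SD. The result rests on an assumed two-sided alpha of 0.05, but alpha 0.001 does not rescue the printed figures. It also rests on analysing all cells, as the protocol describes.

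The mismatch between a 30% loss and the minimum of 8 is a small internal inconsistency that needs no modelling. It does not mean that the trial loses power at a 30% loss.

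The error is conservative: nothing here shows the trial to be underpowered for 0.3 SD. This is a correction that should be made, not a threat to the trial.

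**What to change.** - Re-run the calculation with 99 clusters, 33 per step and four rounds, under the planned model.
- Restate power and the detectable effect for 8 and 11 children, naming the alpha, the cluster autocorrelation and the handling of the transition cells. If the original figures relied on dropped cells or an autocorrelation below 1, say so, and reconcile that with Table 1 and the analysis model.
- Restate the tolerated loss from the corrected calculation. Changing 30% to 27% (3/11 = 27.3%) would only align it with a minimum of 8 that the inputs do not support.

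The cost is one re-run and one edited paragraph. No change in enrolment is needed.
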